### Data Collection and Statistical Analysis

Data will be obtained before the fMRI, 3 months after completing the IET, and 12 months after the fMRI. Data will be compared between the groups (IET vs treatment as usual in control groups A and B). The data will be analyzed using a repeated-measures analysis (mixed models).

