**Methods:**

We present a novel method aiming to prevent the transition from subacute to chronic back pain by altering the emotional response to pain using an IET. In this pilot randomized controlled trial, participants who are at a higher risk of LBP chronification due to the presence of a biomarker (ie, functional connectivity between the medial prefrontal cortex and nucleus accumbens) will be randomly assigned to the IET intervention group or control group A (treatment as usual). Participants who do not present with the biomarker will be assigned to control group B (treatment as usual) to assess how well this biomarker predicts the chronification of subacute LBP in this study population. Questionnaires measuring the pain experience and psychological distress will be used before the intervention, after the intervention (at 3 months), and at the 12-month follow-up.

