### Functional Connectivity Analysis and Participant Grouping

The functional mPFC-NAc connectivity of each participant will be analyzed with data processing assistant for resting-state fMRI [29]. Slice timing correction will be performed using the first acquired slice (slice number 2) as the reference slice. Images will be realigned, and normalization will be completed using a new segment and the diffeomorphic anatomical registration through exponentiated lie (DARTEL) algebra algorithm [30]. Images will be smoothed by DARTEL using a Gaussian kernel of full width at a half-maximum of 5 mm. Nuisance covariate regression will be performed with the Friston 24-parameter model. White matter signals and cerebrospinal fluid signals will be used as covariates. A 0.01 to 0.1 Hz filter will be applied. The functional region of interests, defined according to the criteria of Baliki et al [28], are spheres with a 10-mm radius. Talairach seed coordinates for the mPFC (x=2, y=52, z=–2) and right NAc (x=10, y=12, z=–8) will be transformed into Montreal Neurological Institute coordinates before calculating mPFC-NAc synchronicity. Participants with z(r) ≥0.25 will be classified as having an increased risk for LBP chronification.

Participants who are found to have a higher risk of pain chronification due to the presence of a biomarker (mPFC-NAc synchronicity) will be randomized to the intervention group (IET) or control group A (treatment as usual). To assess how well this biomarker predicts the chronification of LBP, participants who are not found to have the biomarker will be assigned to control group B (treatment as usual).

Participants who fit the inclusion criteria (based on fMRI) will undergo a lumbar spine MRI examination (1.5 Tesla) to rule out specific causes of the low back symptoms (ie, tumors, evidence of ankylosing spondylitis) or other conditions requiring special attention. Furthermore, the lumbar MRI ensures the homogeneity of the study population. The feedback from the MRI examination will be given to the participants by the clinician briefly in the style of “no specific causes or special factors to be taken into account,” after which the participants will participate according to the protocol. If necessary, proper further examinations and treatments will be provided, and the participants will be excluded from the study.

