### Study Procedure

The study procedure is outlined in Figure 1. All participants will complete the study questionnaires before the fMRI, 3 months after completing the IET, and 12 months after the fMRI. Questionnaires will be presented in paper form. Post-IET questionnaires will be sent to participants by paper mail. Questionnaires will be pseudonymized.

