**Figure 1 figure1:**
[figure not shown]
The study procedure. fMRI: functional magnetic resonance imaging; IET: interoceptive exposure technique; LBP: low back pain; MRI: magnetic resonance imaging.

Participants at risk for LBP chronification will be classified and categorized within 48 hours after fMRI. High-risk participants will be further pseudo-randomized into the intervention (IET) or control group (A), whereas low-risk participants will form the treatment-as-usual group (B). Participants will be provided with group-specific instructions on the remaining study procedures by email and telephone. Participants in the intervention group will begin practicing the IET within a week after neuroimaging.

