### Study Setting

The IET to be used in this study is a modified version of the IET used by Flink et al [31]. The original Swedish version used in the original study was translated into Finnish with small adjustments to the IET without departing from the structure and scope of the original exercise. At the beginning of the study procedure, the participants will be given brief information about the IET. The participants will access the IET through a web-based platform secured by a personal password and a username. The platform can be accessed on a mobile phone or a home computer with internet access. The participants will then be told to perform the 8 minutes and 26 seconds–long IET exercise 3 times a week (Monday, Wednesday, and Friday) in as serene a setting as possible. During the IET, the participants will be asked to relax and calmly focus their attention on the sensation of pain. They will be told to focus on the pain with an open and nonjudgmental attitude and to feel the pain as much as possible without trying to change it or block it. If their attention wanders from the pain, they will be asked to return their focus to the pain sensation. The web-based exercise platform will keep track of the participant’s activity. Platform visits and the time spent committing to the IET will be recorded. In this way, the research team can contact the participant if he or she is not logging on to the platform or if the IET is not carried out completely. The participant will be reached by phone to investigate the problem with attendance. If the participant misses 3 consecutive training sessions (ie, 1 week’s training), he or she will be excluded from the study. The IET intervention is designed to take 12 weeks. The IET exercise (in Finnish) is presented in Multimedia Appendix 1.

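### The middle questionnaire is timed from completion of the IET, a date that neither control group has, and the abstract appears to place the same visit about three months earlier

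*Protocol article*

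**What the plan says.** Three places in the article time the middle of the three assessments.

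- Abstract, Methods paragraph: questionnaires are given "before the intervention, after the intervention (at 3 months), and at the 12-month follow-up". The origin of the 3 months is not stated.
- Study Procedure: "All participants will complete the study questionnaires before the fMRI, 3 months after completing the IET, and 12 months after the fMRI".
- Data Collection and Statistical Analysis: "Data will be obtained before the fMRI, 3 months after completing the IET, and 12 months after the fMRI".

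Two further statements fix the calendar of the IET arm. Study Setting says: "The IET intervention is designed to take 12 weeks". The text under Figure 1 says: "Participants in the intervention group will begin practicing the IET within a week after neuroimaging".

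The section on functional connectivity analysis and participant grouping gives treatment as usual to both control groups: A (biomarker present, randomized) and B (biomarker absent, not randomized). The statistical section then compares IET with A and B in a repeated-measures mixed model. The baseline and 12-month assessments are both tied to the fMRI, which every participant has.

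**The concern.** Of the three assessments, only the middle one is tied to an event that occurs in a single arm. The Study Procedure sentence covers all participants, yet two of the three groups cannot apply it as written. Whoever prepares the mailings for groups A and B must supply a date that the text does not give. The abstract offers one candidate (3 months), and the methods wording, carried over by analogy, offers another (about 6 months).

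The stake is the between-group comparison at that visit. The model has two post-baseline occasions, and the article does not name either as the one at which the primary outcome, NRS pain intensity, is judged. If a visit label stands for different elapsed times in different arms, the arm contrast at that visit mixes the treatment effect with whatever pain does over the extra weeks. Randomization between IET and group A does not protect against this, because the difference would arise after allocation. With 7 per randomized arm in the pilot, there is little scope to adjust for it afterwards. The aims carry the same parameters into the full-scale study of 20 per arm.

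A second matter is what is being estimated. An end-of-treatment assessment and one made 3 months later answer different questions, and the article should say which it intends.

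**Working it through.** **Inputs**

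- IET start: 0 to 7 days after fMRI (text under Figure 1).
- IET length: 12 weeks = 12 × 7 = 84 days (Study Setting).
- Follow-up interval: 3 months (Study Procedure; Data Collection and Statistical Analysis). With a month of 365.25/12 = 30.44 days, 3 months = 91.3 days = 13.0 weeks.

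**Step 1: end of IET, counted from fMRI**

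End = start + 84 days.

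- Earliest: 0 + 84 = day 84 (12.0 weeks, 2.8 months).
- Latest: 7 + 84 = day 91 (13.0 weeks, 3.0 months).

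This reproduces the abstract's 3 months if the abstract means the end of treatment.

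**Step 2: 3 months after completing the IET, counted from fMRI**

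Visit = end + 91.3 days.

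- Earliest: 84 + 91.3 = day 175 (25.0 weeks, 5.8 months).
- Latest: 91 + 91.3 = day 182 (26.0 weeks, 6.0 months).

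This does not reproduce 3 months from fMRI under either start date.

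**Step 3: distance between the two timings**

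- Day 175 − day 91 = 84 days (12 weeks).
- Day 182 − day 91 = 91 days (13 weeks).

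**Step 4: which groups can apply the rule**

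| Assessment | Anchor in the methods | IET | A | B |
|---|---|---|---|---|
| Baseline | before fMRI | yes | yes | yes |
| Middle | 3 months after completing IET | yes | no such date | no such date |
| 12 months | after fMRI | yes | yes | yes |

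**Step 5: what unequal timing would do**

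Let m(t) be the mean pain score without IET at t weeks after fMRI. Suppose IET is assessed at t1 and group A at t0. Then the contrast at that visit contains the treatment effect at t1 plus m(t1) − m(t0). The second term is zero if t1 = t0. Otherwise its sign and size depend on m between about week 13 and week 26, and the documents give no rate of change there. The comparison with group B contains a similar timing term, on top of the prognostic difference that the biomarker is meant to capture.

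**The case against.** The strongest reply is that the article intends one common visit and words it loosely. The two full statements of the schedule agree with each other. The abstract's phrase, "after the intervention (at 3 months), and at the 12-month follow-up", can be read as a compressed form of 3 months after the intervention. Because the IET has a fixed designed length and a start within a week, a matching control date of about 25 to 26 weeks after fMRI can be worked out. Figure 1 is not available here and may show a timeline by group. This is also a condensed article, and a mailing calendar is detail that a full protocol can hold.

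Much of this stands. The conflict with the abstract is probable, not certain. A reader might infer that controls are to be assessed at 3 months and IET participants at about 6, so that natural recovery will pass for benefit. The documents do not support that: no section pairs the earlier date with controls and the later one with IET. Nor does the introduction establish recovery in the relevant window. It says that episodes usually improve within weeks, but the same sentence adds that pain and disability typically continue and that recurrences are common. Participants enter with 4 to 10 weeks of pain. If the scan follows promptly, weeks 13 to 26 after fMRI correspond to about 17 to 36 weeks of pain (4 + 13 to 10 + 26), and the randomized participants are selected for predicted chronification. Any figure for spurious benefit in NRS points would therefore be invented.

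A reader might also infer that IET participants who pause have no usable date. The rule in Study Setting that excludes anyone missing three consecutive sessions largely closes that gap.

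One point survives the reply. The article does more than omit a control date: it states a rule for all participants that groups A and B cannot follow, however the abstract is read.

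**Conclusion.** The point holds as an inconsistency in the stated schedule that should be fixed before enrolment. It is not a demonstrated bias.

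- Firm: the middle visit is anchored to an event that two of the three groups never have, and the text shown supplies no substitute. A timeline in Figure 1 could supply one, but it would not correct the wording of the two methods sections.
- Probable: the abstract and the methods give different times, about day 84 to 91 against about day 175 to 182 after fMRI. This rests on reading the abstract's 3 months as the end of a 12-week course begun within a week of the scan.
- Conditional: if the arms were assessed at different elapsed times, the two stated timings would put them up to about 12 to 13 weeks apart, and timing would be confounded with treatment at that visit. Neither the direction nor the size of the effect on pain can be derived from the documents.
- Not affected: baseline and the 12-month visit, which are common to all arms.

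**What to change.** Reconcile the abstract, Study Procedure, and Data Collection and Statistical Analysis in two steps.

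1. State whether the middle visit is an end-of-treatment assessment or one made 3 months later. On the article's own calendar, an IET participant who starts on the last permitted day reaches these at about 13 and about 26 weeks after fMRI respectively. The choice is the sponsor's.
2. Define that visit for IET, A and B alike as the same number of weeks after the fMRI (or allocation) date, with one common window, and drop completion of the IET as the anchor. For example: *In all three groups, the middle questionnaire falls due N weeks from the fMRI date, within a stated window.*

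Keep the 12-month visit as written.

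The cost is a wording change in three places and a mailing calendar run from the fMRI date. Follow-up questionnaires already go by post, so participants carry no extra burden, and the article reports no enrolment as of September 2023. Once questionnaires have been collected at unequal times, the comparison at that visit could not be repaired.

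### The one stated comparison sets IET against control groups A and B without separating them, although B is a non-randomised low-risk group; pooling it with A would bias the efficacy estimate against IET

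*Protocol article*

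**What the plan says.** Randomisation covers biomarker-positive participants only. The Abstract says that they "will be randomly assigned to the IET intervention group or control group A (treatment as usual"). Aims and Objectives puts 7 in each of these two pilot groups and plans 20 and 20 for a full-scale study with the same parameters.

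Control group B is formed differently. Under Functional Connectivity Analysis and Participant Grouping, "Participants with z(r) ≥0.25 will be classified as having an increased risk for LBP chronification", and "participants who are not found to have the biomarker will be assigned to control group B (treatment as usual"). The text with Figure 1 adds: "whereas low-risk participants will form the treatment-as-usual group (B"). Aims and Objectives leaves the number in B open. B has a stated purpose: "To assess how well this biomarker predicts the chronification of LBP".

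Data Collection and Statistical Analysis then gives the comparison, "Data will be compared between the groups (IET vs treatment as usual in control groups A and B"), and the method, "The data will be analyzed using a repeated-measures analysis (mixed models"). It does not say whether A and B form one comparator or two. It names neither IET versus A as the efficacy contrast nor A versus B as the biomarker contrast. The Results section says that the design serves both efficacy and replication of the biomarker.

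**The concern.** The stated comparison uses B as a comparator for IET. The rest of the article gives B another job, which is to show whether untreated people without the biomarker fare better than untreated people with it. Every member of B lies on the other side of the biomarker cut-off from every member of IET and A. A contrast that uses B as a control for IET therefore carries the risk difference along with the treatment effect.

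The mixed model does not remove this. All participants enter under the same pain criterion (above 40/100), and the biomarker is expected to separate them later, over one year. That separation would appear as diverging trajectories, the same pattern that a treatment effect produces. Adjusting for baseline pain would not tell the two apart.

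At stake is the efficacy conclusion. A useful intervention could look ineffective or harmful, to a degree that depends on how many low-risk people happen to be scanned.

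**Working it through.** The article gives no alpha, power, effect size or SD, so it has no figure of its own to reproduce. The check concerns which quantity each reading of the sentence estimates.

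**Inputs from the article**
- A has 7 participants in the pilot and 20 in the full-scale study (Aims and Objectives).
- The size of B is undefined (same section).
- The primary outcome is pain intensity on the NRS (Outcome Assessment and Measurements).
- The biomarker is reported as predictive of chronicity at one year with more than 80% accuracy (Introduction, Overview).

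**Assumptions**
- g, the A-minus-B difference in mean NRS pain under usual care: 0.5, 0.8 or 1.5 SD.
- δ, the true benefit of IET over A: 0 or 0.8 SD.
- Number in B: 7 or 14.
- Equal within-group SD, complete data, and no term for biomarker status in the pooled analysis.

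**Formulas.** Let mean pain be μ in A, μ − g in B and μ − δ in IET, and let w = nB/(nA + nB).
- IET versus A: μ − (μ − δ) = δ, with no bias.
- IET versus B: (μ − g) − (μ − δ) = δ − g, with bias g whatever the size of B.
- IET versus pooled A+B: (μ − w·g) − (μ − δ) = δ − w·g, with bias w·g.

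**Pooled reading, pilot, nA = 7**

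| nB | w | g (SD) | bias w·g (SD) | apparent benefit if δ = 0.8 (SD) |
|---|---|---|---|---|
| 7 | 7/14 = 0.50 | 0.5 | 0.25 | 0.55 |
| 7 | 0.50 | 0.8 | 0.40 | 0.40 |
| 7 | 0.50 | 1.5 | 0.75 | 0.05 |
| 14 | 14/21 = 0.67 | 0.5 | 0.33 | 0.47 |
| 14 | 0.67 | 0.8 | 0.53 | 0.27 |
| 14 | 0.67 | 1.5 | 1.00 | −0.20 |

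The bias depends only on w and g. In the full-scale study, 20 in A with 20 in B again gives w = 0.50 and a bias of 0.25 to 0.75 SD.

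**False rejection with no true effect.** With a normal approximation and an assumed two-sided alpha of 0.05, the standard error in SD units is √(1/7 + 1/(7 + nB)) and the test statistic is shifted by w·g divided by that.
- nB = 7: the standard error is √(1/7 + 1/14) = 0.463. The shift is 0.25/0.463 = 0.54 to 0.75/0.463 = 1.62, and the rejection rate is 0.08 to 0.37.
- nB = 14: the standard error is √(1/7 + 1/21) = 0.436. The shift is 0.333/0.436 = 0.76 to 1.00/0.436 = 2.29, and the rejection rate is 0.12 to 0.63.

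These rejections would point mainly towards harm from an inert intervention.

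**Separate reading.** With a three-level group factor, IET versus A recovers δ. IET versus B gives δ − g: with δ = 0.8 this is 0.3, 0.0 and −0.7 SD for g = 0.5, 0.8 and 1.5.

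**The case against.** The strongest reply is that pooling is never stated and is not the most natural reading. The sentence speaks of groups in the plural, Strengths and Limitations describes a three-group design, and A and B are defined separately throughout. The pilot numbers are fixed for IET and A only, and the full-scale study has a single control group, which suggests that IET versus A is the intended efficacy comparison. This stands. A reader might infer that the efficacy result is confounded however B is handled, but the article does not support that: with A and B as separate levels, IET versus A is the randomised contrast and is unbiased.

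A reader might also infer that the biomarker aim has no comparison at all. That goes too far. The contrast is not named, but a three-group model could yield A versus B.

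On size, it is tempting to turn the cited accuracy into chronicity rates of, say, 80% and 20%. Overall accuracy does not fix the rate in either group, and the primary outcome is NRS pain, not a chronicity proportion. The Introduction also says that biomarkers have so far predicted chronic back pain insufficiently, so g could be small.

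Finally, listing every contrast is commonly left to a fuller document. That excuses brevity, but it does not cover this sentence, which states a comparison that does not fit the purpose given to B.

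**Conclusion.** The point holds in conditional form. The stated comparison does not match the role of B and leaves the biased readings open. If A and B are pooled, the efficacy estimate is off by w·g: 0.25 to 0.75 SD with 7 in B and 0.33 to 1.0 SD with 14, for 7 in A and an assumed g of 0.5 to 1.5 SD. If IET versus B is read as efficacy, the bias is g itself. The direction is against IET provided that the biomarker is prognostic as reported; if g is zero, there is no bias. The values of g and the sizes of B are assumptions, because the article gives neither. The randomised IET-versus-A contrast remains sound if A and B are kept apart.

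**What to change.** In Data Collection and Statistical Analysis, replace the parenthesis with two named contrasts:

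1. Efficacy: IET versus A only, as randomised among biomarker-positive participants.
2. Biomarker: A versus B, both under usual care, with the IET arm excluded from this contrast.

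Add that A and B are not pooled for efficacy and that any IET-versus-B comparison is descriptive only. B need not be removed from the model: a three-level group factor is acceptable if the IET-versus-A contrast is prespecified.

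The cost is one paragraph of wording and no new data. The article reports no enrolment as of September 2023. Because the full-scale study is to reuse the pilot's parameters, settling the wording now also keeps the ambiguity from carrying over.

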### Ethics Approval

This study has obtained ethical approval from the ethical committee at Helsinki and Uusimaa Health District (HUS/2435/2017). Good research ethics practices will be maintained in the study according to the Declaration of Helsinki.

There will be no inclusion of vulnerable groups (ie, children, prisoners, individuals with mental disorders). No participant reimbursement will be provided to prevent economic factors from impacting the recruitment process. No specific physical health risks can be seen to be involved in participating in the study. Participants will be physically checked with a handheld metal detector before entering the scanner. However, the procedure could cause slight stress for participants and might even provoke pain. The fMRI and MRI procedures could cause some distress for some participants. The IET training might test participants’ motivation.

Anonymity and confidentiality will be ensured by using numerical codes for the participants. Only the research group members will know the participants’ names. Data protection and storage security will be ensured by storing the participant information and questionnaires in a locked cabinet at Orton. Data will be stored behind electronic passwords securely on Orton’s server.

For the duration of the fMRI measurements, all participants will have patient insurance against possible injuries.

